### Outcome measures

2.13

The main outcome measurement will be the pain levels of both rest and mobile status for the BCT patients (the mobile status includes cough, deep breath, and turn over on the bed). The patient will measure their pain according to 3 subjective pain scales, namely the NRS, and FRS before treatment, 30 minutes after treatment and 4 days after the press tack needles/placebo intervention. Furthermore, a follow-up will assess the NRS pain scale telephonically at 14 days and 3 months after the initial intervention.

Secondary outcome measurements will include the improvement of respiratory function, sleep quality, and amount of medication used (specifically analgesics and muscle relaxants). We used the portable triflow flowmeter and VSH sleep scale as objective tools for the aforementioned purposes. The patients will be educated on the use of the flowmeter by the affiliated thoracic surgeon. Patients will be allowed as much time as needed to practice the use of the flowmeter before the first measurement is taken. When the patient is ready, the study personnel will commence the measurements of 3 attempts, and will record the best 2 attempts. The triflow flowmeter measures the amount of air the patient can exhale; it has 3 chambers with their own balls that require air pressures from 600 to 1200 cm^3^ per second to elevate. 1200 cm^3^ is the highest score and indicates good exhalation power. The above process will be done before intervention, 30 minutes after intervention and 4 days after the intervention. The patient will also answer the VSH sleep scale in Mandarin to evaluate the sleep quality of the night before the clinic visit. They will complete the questionnaires accordingly at every clinic visit, for a total of 2 times (on day 1 and day 4). Finally, on the 4th day after the initial intervention, participants will bring back the prescribed medication, including analgesics and/or muscle relaxants that were left unused, to be measured for the amount of medication used.

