### Statistical analysis

2.19

Statistical analyses will be performed using SPSS software version 22.0 (SPSS Inc, Chicago, IL). The demographic data between Acu and Con groups including gender, age, and clinical characteristics will be compared using the Student's *t* test and Chi-squared test. Between-group values will be measured by the paired *t* test. For the multiple pain scale and sleeping quality measurements, a one-way ANOVA will be used according to the previous similar study.^[11]^ We will also implement the advanced repeat measurement analysis in the study. Data will be presented as mean ± standard deviation. A *P*-value of less than .05 will be considered statistically significant.

Subgroup analysis will be done based on the following: age, sex, number of treatments complete, number of hours of needle retention, number of rib fractures, pulmonary complications, hospitalization, number of days from patient's injury to the first treatment, Triflow score, medication use, body mass index, and ISS. In cases of small sample size, the Mann–Whitney *U* and the Wilcoxon sign rank test will be implemented accordingly. Missing data will be analyzed using the pairwise deletion method.

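### The main pain outcome is a bundle of 10 to 24 arm comparisons with no single primary, all judged at P < .05

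*Protocol article*

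**What the plan says.** Section 2.13 of the protocol article defines the main outcome: "The main outcome measurement will be the pain levels of both rest and mobile status for the BCT patients". It then explains that "the mobile status includes cough, deep breath, and turn over on the bed". The scales and clinic times follow: "according to 3 subjective pain scales, namely the NRS, and FRS before treatment, 30 minutes after treatment and 4 days after". Three scales are announced and two are named. The same paragraph adds that "a follow-up will assess the NRS pain scale telephonically at 14 days and 3 months after the initial intervention". None of these scales, states or times is singled out.

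Section 2.19 (Statistical analysis) sets one threshold for everything: a P "value of less than .05 will be considered statistically significant". For the pain data it says: "For the multiple pain scale and sleeping quality measurements, a one-way ANOVA will be used according to the previous similar study". It also mentions a repeated-measures analysis, without tying it to a scale, state or contrast.

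Section 2.16 (Sample size calculation) works from the pain reduction seen immediately after treatment in an earlier trial. It does not say which scale or state that was, and it does not declare the 30-minute score to be primary.

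**The concern.** The Introduction's hypothesis is only that true press tacks relieve pain better than placebo tacks. With a bundled main outcome and one blanket threshold, the text does not stop any single favourable cell from being presented as confirming that hypothesis. The cell could even be chosen after the codes are broken. The trial's one confirmatory claim would then carry an error rate that nobody has fixed. A reader of the results could not tell whether the reported pain score was the one always intended.

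**Working it through.** **1. The plan's own figure.** Section 2.16 gives at least 18 per group for 95% power at an effect size of 1.124365. A two-sample t test with one-sided alpha 0.05 needs 17.84, so 18 per group. With two-sided alpha 0.05 it needs 21.57, so 22. The stated 18 therefore reproduces as a one-sided test of a single comparison. The final 36 per group less 20% dropout leaves 36 × 0.8 = 28.8, about 29 evaluable.

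**2. Counting the comparisons** (inputs from 2.13: 2 named scales, rest plus 3 manoeuvres, 2 clinic times, 2 NRS telephone times).

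- Four states, all asked by telephone: 2 × 4 × 2 + 1 × 4 × 2 = 24
- Four states in clinic, one NRS rating per call: 16 + 2 = 18
- Mobile pain as one rating, both states asked by telephone: 2 × 2 × 2 + 1 × 2 × 2 = 12
- Mobile pain as one rating, one NRS rating per call: 8 + 2 = 10

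**3. Familywise error if each cell is tested at 0.05 and any one suffices.** With independent tests it is 1 − 0.95^k. Pain ratings from the same patient are correlated, so correlated normal test statistics were also simulated. The correlation between two cells was the product of a scale, a state and a time factor, each applied only where the cells differ. The factors are assumptions; the documents give none. The columns run from the strongest setting (scale 0.95, state 0.9, time 0.8) to the weakest (0.8, 0.6, 0.4), with a million runs per entry.

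| Comparisons | Independent, two-sided | Correlated, two-sided | Correlated, favouring acupuncture (nominal 2.5%) |
|---|---|---|---|
| 24 | 70.8% | 22.9-50.8% | 11.5-26.5% |
| 18 | 60.3% | 20.0-41.8% | 10.0-21.5% |
| 12 | 46.0% | 17.8-34.1% | 8.9-17.4% |
| 10 | 40.1% | 16.4-29.9% | 8.2-15.1% |

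**4. If a repeated-measures test merges the time points.** One test per scale and state remains: 2 × 2 = 4 or 2 × 4 = 8. With a common correlation between tests of 0.5 to 0.8, the two-sided rate is 15.6% down to 11.3% for 4 tests and 24.9% down to 15.7% for 8.

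**5. If the telephone scores are not part of the main outcome.** The clinic cells alone number 8 or 16. With the same common correlation, the two-sided rate is 15.7-24.9% for 8 and 20.8-37.6% for 16.

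**6. After the fix.** One pre-named comparison has a 5% error rate. At the planned effect size, 29 per arm gives 98.8% two-sided power. Keeping all 24 with a Bonferroni limit of 0.05/24 = 0.00208 would leave 84.6% power per comparison.

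**The case against.** A reader might infer that the protocol plans 24 separate tests and so carries a 71% chance of a false efficacy claim. The document does not support that.

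- It gives no count. The manoeuvres appear in a parenthesis that explains mobile status, so a single mobile rating fits the wording. For the calls, only the NRS is mentioned, not how many states are asked.
- It does not say that each cell gets its own test, and the repeated-measures analysis could merge time points.
- It does not say that one significant cell is enough. Asking for pain in both states could be read as requiring both.
- The 71% assumes independent tests, which is implausible for two pain scales scored by the same patient at the same visit. It also counts false results favouring placebo, which could not support the hypothesis.

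These points stand, and they are why the size is given as a range and in one direction as well.

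It can also be said that adjustment and testing order may sit in an analysis plan that is not shown. That is fair, and the absence of an adjustment method is not the point made here. The main outcome, however, is defined in this article, and it is defined as a bundle. The sample size basis comes closest to indicating a primary time point, but 2.16 does not call it primary, and 2.13 lists 30 minutes and day 4 side by side.

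**Conclusion.** The point holds as a defect in how the main outcome is fixed: no single pain scale, state or time point is primary, and one P < .05 rule covers them all. Under cell-by-cell testing where any one success counts, the two-sided familywise error is about 16-51% for 10 to 24 comparisons, at least about three times the nominal 5%. In favour of acupuncture it is about 8-26% against 2.5%. With time points merged it is about 11-25% two-sided, at least about twice nominal. The percentages rest on assumed correlations and on the any-one-suffices rule, which the protocol neither states nor excludes. That the error is inflated does not depend on which count is right. A rule requiring both states to succeed would lower the rates, but the protocol would have to state it.

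**What to change.** Before unblinding, amend 2.13 and 2.19 to name one primary pain endpoint: one scale, one state or a pre-defined movement composite, and one time point, tested at two-sided 0.05. Two candidates are the NRS at 30 minutes (with its state named), to which the sample size basis is closest, and movement-evoked NRS at day 4. Either would do, but only one should be chosen. Make every other combination of pain scale, state and time secondary, either in a fixed testing sequence or reported with confidence intervals and no confirmatory claim. Align the registry entry if it differs. Reconcile the three scales announced in 2.13 with the two named; a third scale scored at both clinic times would add up to 4 × 2 = 8 cells.

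The cost is a change of wording, with no extra patients or visits. The downside is that the other pain results can no longer carry the headline claim.

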**Methods::**

The study is designed as a double-blind randomized control trial. We will include 72 patients divided into 2 groups; the acupuncture group (Acu) and placebo group (Con). The acupuncture group will receive true acupuncture using a uniquely designed press tack needle. The control group will receive placebo acupuncture treatment through the use of a similarly designed press tack needle without the needle element. The acupoints selected for both groups are GB 34, GB 36, LI 4, LU 7, ST 36, and TH 5. Both groups will receive 1 treatment only following the initial visit to the medical facility and upon diagnosis of BCT. Patient outcome measurements include: Numerical Rating Scale, Face Rating Scale, respiratory function flowmeter, Verran Snyder-Halpern sleep scale, and the total amount of allopathic medication used. Follow-up time will be scheduled at 4 days, 2 weeks, and lastly 3 months.

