### Participants

2.2

We will include a total of 72 patients who are suffering from BCT. After the patient's accident, such as falls, kicks, fights, or traffic accidents, they will be sent to the emergency room and visit a chest surgical out-patient clinic for treatment and follow-up. Those who meet the inclusion criteria will be informed about the study and can freely choose to participate. They will sign the informed consent and will be randomized accordingly, with commencement of the study occurring immediately. The patients are allowed to drop out from the study at any time point of the study.

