### Inclusion criteria

2.3

Age 20 to 80 years old.Patients who have chest trauma as described by themselves or based on medical chart records within 1 week of injury.Injury Severity Score (ISS) is less than 18 points.Body mass index < 30.

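### For any patient treated on the day of injury, the day-1 sleep score describes a pre-injury night, so the day 1 to day 4 change mixes the onset of injury with the effect of treatment

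*Protocol article*

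**What the plan says.** Section 2.13 (Outcome measures) makes sleep quality a secondary outcome, worded as an improvement and measured with the VSH scale: "The patient will also answer the VSH sleep scale in Mandarin to evaluate the sleep quality of the night before the clinic visit". The scale is answered at two visits, day 1 and day 4.

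Section 2.3 (Inclusion criteria) sets the entry window: "Patients who have chest trauma as described by themselves or based on medical chart records within 1 week of injury". It gives an upper limit but does not require that a night has passed since the injury.

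Section 2.2 (Participants) describes the route to the first visit: "they will be sent to the emergency room and visit a chest surgical out-patient clinic for treatment and follow-up". The delay between the two is not stated. Consent and randomisation follow, "with commencement of the study occurring immediately". The abstract likewise ties treatment to the first visit and the diagnosis.

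Section 2.19 (Statistical analysis) names a one-way ANOVA for sleep, a paired t test and a repeated-measures analysis. Days from injury to first treatment is listed there as a subgroup variable, not as an adjustment.

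**The concern.** The day-1 score is meant to show how the patient slept with the injury before treatment. For a patient seen on the day of the accident it shows a normal night instead. The day-1 column therefore holds two different quantities, with nothing to tell them apart.

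The introduction says that pain from the injury may prevent sufficient sleep, and section 2.1 states the aim as better sleep after the trauma. A pre-injury night cannot serve as the starting point for that improvement. A same-day patient who gains from treatment may still show a worse score on day 4 than on day 1. An analysis plan written later can identify these patients from the injury date, but it cannot supply a post-injury baseline that was never collected.

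**Working it through.** **The plan's own figure.** There is none for sleep. The sample size in section 2.16 rests on pain and has no bearing here.

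**Which night is rated.** The timing follows from sections 2.2, 2.3 and 2.13.

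- First visit on the day of injury: the day-1 rating covers a night before the injury.
- First visit after at least one night: the day-1 rating covers a night after the injury.
- The day-4 rating covers a night after injury and treatment for everyone.

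The change is therefore (injured, treated night) minus (usual night) in same-day patients, and (injured, treated night) minus (injured, untreated night) in the others.

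**Size of the mixture.** All inputs are assumed, because the protocol gives none of them: s is the share of same-day patients, D the sleep loss caused by injury in SD units, and 0.5 the correlation between day 1 and day 4.

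- Variance of the change without mixture: 2 × (1 − 0.5) = 1 SD².
- With mixture: 1 + s(1 − s)D².
- Equivalent loss of patients in a change-score analysis: 1 − 1/variance.
- Shift of the mean change within each arm: −s × D.

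| s | D | Variance factor | Equivalent loss | Within-arm shift (SD) |
|---|---|---|---|---|
| 5% | 1 | 1 + 0.0475 = 1.05 | 4.5% | −0.05 |
| 10% | 1 | 1 + 0.09 = 1.09 | 8% | −0.10 |
| 50% | 1 | 1 + 0.25 = 1.25 | 20% | −0.50 |
| 10% | 1.5 | 1 + 0.2025 = 1.20 | 17% | −0.15 |
| 30% | 1.5 | 1 + 0.4725 = 1.47 | 32% | −0.45 |
| 50% | 1.5 | 1 + 0.5625 = 1.56 | 36% | −0.75 |

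**Effect on the comparison of arms.** This was simulated with 36 patients per arm and 4,000 runs per setting. Assumptions: D = 1, correlation 0.5, untreated day-4 sleep 0.6 SD below usual, true treatment effect 0 or 0.5 SD. The expected control-arm change is −0.6 − 0 = −0.6 SD in same-day patients and −0.6 − (−1) = +0.4 SD in the others.

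With a true effect of 0.5 SD:

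| s | Control-arm mean change | Estimated arm difference in change | Power, change score | Power, day 4 alone | Power, day 4 adjusted for day 1 as recorded |
|---|---|---|---|---|---|
| 0% | +0.4 | 0.495 | 55% | 57% | 68% |
| 10% | +0.3 | 0.494 | 52% | 55% | 65% |
| 20% | +0.2 | 0.501 | 50% | 56% | 66% |
| 30% | +0.1 | 0.500 | 48% | 56% | 65% |
| 50% | −0.1 | 0.504 | 48% | 56% | 65% |

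With a true effect of 0, the estimated difference stays within 0.005 SD of zero and the change-score test rejects in 4.4% to 5.5% of runs. The simulation error on a power near 50% is about √(0.5 × 0.5/4,000) = 0.8 percentage points.

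The within-arm mean falls and finally changes sign as s rises, while the between-arm difference does not move. The loss of power is clearest for the change score and only about 2 to 4 points when day-1 sleep is a covariate. The model with the pre-injury indicator and its interaction was not simulated.

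**The case against.** A reader might infer that the change in same-day patients reflects the injury and not the treatment, or that the sleep result of the trial is biased. The documents do not support either. The change contains both components. Allocation is random 1:1 (section 2.6), the placebo group follows the same course and recording (section 2.11), and the hypothesis is superiority over placebo. The pre-injury shift is equal in expectation in both arms and cancels. The shift of −s × D belongs to the within-arm mean only.

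Chance imbalance in the same-day share is not a separate harm. It is part of the added variance, and the error rate of the test already covers it.

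The share may also be small. Patients pass through the emergency room before an out-patient clinic, and the delay is not given. The larger losses in the first table depend on D = 1.5 and on shares that nothing in the protocol supports or excludes.

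Two further points stand in part. The planned subgroup by days from injury shows that same-day patients will be identifiable, but it does not correct the baseline. And section 2.19 does not commit to change from day 1 as the sleep analysis. However, 2.13 words the outcome as improvement, and 2.19 names paired and repeated-measures methods, so a before-after reading is a likely use of the data.

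**Conclusion.** The point holds in a limited form. The recall night, the open lower end of the entry window and the immediate start together give a pre-injury baseline to anyone treated on the day of injury, and nothing in the protocol flags or adjusts for it. For these patients the day 1 to day 4 change cannot be read as improvement, and an arm's mean change is pulled down by their share.

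The treatment comparison remains valid and loses only precision. The variance factor for a change score runs from about 1.05 (s = 5%, D = 1) to 1.56 (s = 50%, D = 1.5) at correlation 0.5, all assumed values. In the simulation with D = 1, change-score power falls from 55% to between 48% and 52%. Sleep is a secondary outcome, so this is an inexpensive improvement to the plan and not a threat to the main result.

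**What to change.** In section 2.13, add that the day-1 form records whether the rated night preceded the injury, or that this is derived from the injury date.

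In section 2.19, define the sleep outcome as the between-arm comparison of day-4 VSH, adjusted for day-1 VSH, the pre-injury-night indicator and their interaction. Every patient with both ratings then stays in the analysis, and the day-1 score may predict day 4 differently in the two kinds of patient. State that day 1 to day 4 change will not be reported as improvement in patients whose rated night preceded the injury.

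The cost is one tick box or derived variable, two extra model terms and a few sentences. The injury date is already needed for the entry window and for the subgroup by days from injury. Same-day patients will have no before-after sleep result. If they are few (5% of 72 is 3.6 patients), the interaction cannot be estimated usefully, so the plan should say in advance when the indicator alone will be used.

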### Follow-up

2.14

After the initial visit to the chest surgical out-patient clinic, the participates in both the Acu and Con groups will be expected to return 4 days after acupuncture/placebo treatments for needles/placebos withdrawal along with chest plain film, NRS, FRS scores, flowmeter, respiratory function, VSH sleep scale assessments, and amount of medication used. On the 14th day and at 3 months after the initial intervention, a study personal will arrange a telephonic consultation to enquire about the pain scale (NRS) and any adverse effect related to the acupuncture treatment and the chest trauma (Fig. 4).

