### Acupuncture group (Acu)

2.10

The patient will lay down in a supine position on the treatment bed and allowed an adaptive relaxation period of 5 minutes. The acupuncturist will start to sterilize the specific body surface areas over the acupoints with a 70% alcohol pad. Accordingly, the bilateral acupoints of GB 36 (Waiqiu), GB 34 (YangLingQuan), ST 36 (Zusanli), LI 4 (HeGu), LU 7 (LieQue), TH 5 (Waiguan) were chosen for both groups. Each patient will receive 12 press tack needles in total. The needle's depth of insertion will be 0.6 mm. The acupuncturist will manually press the press tack needles over the above-mentioned acupoints without any needle manipulation or “De Qi” sensation. The participants will lay on the treatment bed for the duration of 30 minutes. After the aforementioned process, the vital signs, pain levels, and flowmeter will be recorded again to represent the immediate effect after acupuncture. Finally, the acupuncturist will educate the patients about the total number of press needles and the allotted time of retention. The press tack needle retention time will total 4 consecutive days.

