### Adverse events

2.15

Before the enrollment of the study, the participants or the patient's legal guardian will be informed about acupuncture adverse events including bleeding, hematoma, infections, alcohol allergy, pneumothorax, etc. In any case of acupuncture related serious adverse events occurring, these will be reported immediately to the primary investigator and the institutional review board. We will collect all the adverse event details such as: treatment site, acupuncture points selected, patient recovery outcome, number of events, etc. Acupuncture will be stopped and treatment groups will be un-blinded. We will also provide suitable treatment, including hospitalization for the patients.

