
### Limitations

3.1

The study provides an effective intervention but is limited to a shallow acupuncture needling depth of the superficial subcutaneous layers and cannot be associated with the benefits caused by the deeper stimulations commonly associated with most acupuncture interventions. Furthermore, the point selection in this study only concentrates on anterior and lateral BCT locations. Lastly, the follow-up method of telephone calls at 14 days and after 3 months can prove problematic, and a high loss to follow-up is anticipated.

In this study, we offer a simple, low-cost form of acupuncture that, if it will prove superior analgesic effects in comparison to the placebo, can provide a safe and reasonable treatment alternative to BCT patients.

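### In the visible text, adverse effects are asked about only in the day-14 and 3-month telephone calls, after the tacks are out; the 30-minute recording and the day-4 visit name no such enquiry

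*Protocol article*

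**What the plan says.** Section 2.14 (Follow-up) of the protocol article gives an item list for each kind of follow-up contact.

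- **Day 4, in person.** Patients "return 4 days after acupuncture/placebo treatments for needles/placebos withdrawal along with chest plain film, NRS, FRS scores, flowmeter, respiratory function", and the list ends with "VSH sleep scale assessments, and amount of medication used". It has no adverse-event item.
- **Day 14 and 3 months, by telephone.** Both calls are timed from the first application. Their stated content is: "enquire about the pain scale (NRS) and any adverse effect related to the acupuncture treatment and the chest trauma".

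Section 2.10 (Acupuncture group) fixes the exposure: "The press tack needle retention time will total 4 consecutive days". Section 2.11 gives the placebo stickers the same duration. Section 2.10 also describes the recording after 30 minutes on the bed, which covers vital signs, pain and flowmeter.

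Section 2.15 (Adverse events) names haematoma, bleeding, infection, allergy to alcohol and pneumothorax as risks explained to participants. It promises collection of event details, including the site and the points used, and immediate reporting of related serious events. It then states "Acupuncture will be stopped and treatment groups will be un-blinded". It gives no time points and no method for eliciting events.

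Section 3.1 (Limitations) says that the "telephone calls at 14 days and after 3 months can prove problematic, and a high loss to follow-up is anticipated".

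**The concern.** Four of the five named risks (bleeding, haematoma, infection, allergy) can show at the application sites during application or retention. The text places the named enquiry at contacts where the tacks have been gone for some time, the caller cannot see the skin, and the authors themselves expect many patients not to be reached. The two occasions when staff are with the patient and the sites are in view carry no such item.

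This is more than the brevity of an article. The article does state when adverse effects are asked about, and it chooses the less suitable contacts. Minor events that have resolved by day 14 may not be recalled, and a patient who attends on day 4 but is never reached by telephone would have no recorded answer to a safety question. The article closes by suggesting that the device could be a safe option for these patients. That statement needs harms elicited in the same way in both arms and close to exposure.

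**Working it through.** The plan states no figure on this point, so there is none to reproduce. The check sets the contacts side by side.

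| Contact after application | Source | Mode | Tacks in place? | Adverse-effect enquiry named? |
|---|---|---|---|---|
| 30 minutes, day 1 | 2.10 | in person | yes | no |
| Day 4 | 2.14 | in person | until removed at this visit | no |
| Day 14 | 2.14 | telephone | no | yes |
| 3 months | 2.14 | telephone | no | yes |

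**Step 1, count.** An enquiry is named at 0 of the 2 in-person contacts and at 2 of the 2 telephone contacts.

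**Step 2, delay from removal to enquiry.** Retention is 4 days and the calls are timed from the initial intervention.
- First call: 14 − 4 = 10 days after removal.
- Second call, taking 3 months as about 90 days: 90 − 4 = 86 days after removal.

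These delays assume a single application. The abstract gives one treatment and section 2.8 gives two. The text does not say when a second would fall, so the delay from the last removal is unknown under that reading.

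**Step 3, patients with no enquiry at all.** This requires both calls to fail. The Limitations section gives no loss figure, so any number is an assumption. Take 20% to 40% missed at each call, out of 72 patients:
- If the same patients are missed both times: 72 × 0.20 = 14.4 and 72 × 0.40 = 28.8, so about 14 to 29.
- If misses at the two calls are independent: 72 × 0.20² = 2.88 and 72 × 0.40² = 11.52, so about 3 to 12.

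The span of 3 to 29 reflects only the assumed reach and overlap. It is no estimate for this trial, and the conclusion does not use it.

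**Step 4, sections 2.14 and 2.15 together.** Section 2.15 says what to record once an event is known and that related serious events are reported at once. Section 2.14 is the only visible place that says when someone asks. Read together, serious events have a route at any time. Non-serious events have a scheduled prompt only at the calls.

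**The case against.** The strongest case against is that this is a condensed article. Figure 4, which shows the schedule, is not visible, and a full protocol or case report form may well contain an adverse-event check on day 4. That stands as a limit on certainty: it cannot be said that the calls are the only scheduled enquiries in the trial. It does not remove the point, because section 2.14 lists the day-4 items and puts the enquiry elsewhere.

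A reader might infer that local harms will be missed. The documents do not support that. On day 4 the acupuncturist or trained acupuncture nurses remove every tack in clinic, so staff handle each site at the end of exposure. A chest film taken at the same visit could show a pneumothorax. The commitment in section 2.15 to collect event details is not confined to the calls. What remains is that nobody is asked to look, ask or record systematically.

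A reader might also infer that the response "Acupuncture will be stopped and treatment groups will be un-blinded" can never be triggered by planned monitoring. That goes too far. The sentence follows the text on serious events, which are reported whenever they occur, and the 30-minute recording and the day-4 visit are planned contacts at which an event could surface. The text does not say whether stopping concerns one participant or the trial. At trial level, even the later calls could trigger it. If two treatments are given, a further one might exist to be stopped.

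Finally, a reader might infer a biased comparison of harms between arms. Adverse events are not listed among the outcomes and the Statistical analysis section describes no such comparison, so no claim about its bias can be made.

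**Conclusion.** The point holds in limited form. In the visible text, the contacts with a named adverse-effect enquiry are two telephone calls, about 10 and 86 days after removal under a single application, where high loss is anticipated. The in-person contacts at 30 minutes and day 4 name none. The consequence is late, incomplete and unsystematic capture of mainly non-serious local events. Serious events have their own immediate route.

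The size cannot be expressed as a number of patients without assuming a telephone reach that the document does not give. The conclusion rests on the text without Figure 4; if that figure already shows a day-4 adverse-event item, what remains is to bring section 2.14 into line with it. The change is worth making because it is nearly free.

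**What to change.** - In section 2.14 and the schedule, add one standard adverse-event question and a look at the application sites to the existing 30-minute recording and day-4 visit, worded and done identically in both arms.
- On day 4, let the staff who withdraw the tacks do the site check after the outcome scores are taken, so that study nurse 2 does not see skin marks that could hint at allocation.
- Count patients seen on day 4 as assessed for safety, and keep the telephone calls for late events.
- Align sections 2.14 and 2.15, and Figure 4 if it differs, so that timing and content of adverse-event collection agree.
- State in section 2.15 whether the stopping and unblinding sentence applies to a participant or to the trial, and what triggers it. Reconcile the number of treatments in the abstract with that in section 2.8.

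The cost is one or two minutes at visits that already take place, a few lines on the case report form and a short protocol edit. No extra visit, staff or procedure is needed.
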